### Analysis

#### Phase 1

For survey data, Likert scale responses will be coded numerically for qualitative analysis. Descriptive statistics will be calculated to summarize the data, and differences between groups (ie, based on demographic variables) will be explored. For the structured interviews and focus groups, a thematic approach will be used to identify, analyze, and report patterns with the qualitative data. NVivo software will be used, which provides features for coding, organizing, and visualizing data [43]. Both deductive and inductive coding methodologies will be used to link similar codes to broader themes based on significant phrases, concepts, and ideas present in the transcripts [44]. Themes will be reviewed and refined through discussions among the research team to ensure consistency and reliability.

#### Phase 2

The primary outcome will evaluate the impact of the BPA intervention on patients’ progression of ADT use using a generalized linear mixed model to account for matched pairs and random center effects. The model will be adjusted for the number of encounters and other possible confounders not already matched.

The secondary outcome analyses will compare differences in ADT use between non-White and White people with T1D in the intervention and control groups. Additional secondary and exploratory outcomes will be assessed using the appropriate statistical model for the outcome adjusting for patient- and center-level confounders. Exploratory analysis assessing pediatric and adult centers separately will be performed.

In cases where ADT is not prescribed by the provider, we will explore the reasons why, and why the diabetes technology was not offered or accepted by patients. We will quantify the BPA responses as provider-led or patient-led reasons for not advancing ADT use. We will perform multivariable logistic regression analysis to evaluate whether patient characteristics (demographics, race, ethnicity, diabetes characteristics, and complications) are associated with the reasons that technologies are not offered or declined.

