### Control Group

Matched control people with T1D will be selected from the pool of nonintervention clinical centers sharing EMR data with the T1DX-QI coordinating center with over 80,000 people with T1D data available in the database.

To accurately match people with T1D between the intervention and control groups, we will identify and include a comprehensive set of covariates that may influence the likelihood of receiving the BPA. These covariates will include both patient-level and clinical center-level characteristics. Patient-level characteristics will include demographics (age, sex, race, and ethnicity), socioeconomic status (insurance type and zip code–based income), and clinical characteristics (duration of diabetes, comorbidities, HbA_1c_ levels, etc). Clinical center-level characteristics will include clinic size and resources (number of people with T1D seen annually, number and type of clinical full-time equivalents, geographic location, patient population demographics, and historical usage rates of CGMs and AID systems. Intervention and control groups will be matched using the propensity score method.

Before propensity score matching, any missing baseline covariate data will be imputed using predictive modeling techniques. Multiple imputation by chained equations will be used to generate multiple complete datasets, which will then be averaged to create a single dataset for the matching process. This approach ensures that the imputed values are based on observed data, maintaining the integrity and representativeness of the dataset.

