Propensity scores will be estimated using logistic regression, where the outcome variable is the likelihood of receiving the BPA intervention. The model will include the identified patient-level and clinical center–level covariates as predictors. The estimated propensity score represents the predicted probability that a given patient would receive the BPA based on their covariate profile. Patients in the intervention group will be matched to patients in the control group using a 1:4 matching ratio. Nearest neighbor matching without replacement will be used, ensuring that each control patient is only matched once. The matching process will aim to minimize the distance between propensity scores of matched pairs, thus creating comparable groups. The quality of the matching process will be assessed by comparing the distribution of covariates between the matched intervention and control groups. Standardized mean differences will be calculated for each covariate to ensure balance, with a standardized mean difference of less than 0.1 indicating adequate balance. In addition, a visual inspection of propensity score distributions before and after matching will be conducted to confirm the success of the matching process.

To assess the robustness of the results, sensitivity analyses will be performed using different matching algorithms (eg, caliper matching and kernel matching) and varying the matching ratio (eg, 1:3). In addition, the impact of imputation on the results will be examined by comparing outcomes using datasets with and without imputed values.

For nonstatic matching variables (eg, laboratory results), the last available result in the baseline period of 12 months before the BPA deployment date in the intervention centers will be used.

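### The primary model leaves out the matched covariates, although propensity matching balances them only approximately, so residual imbalance stays in the primary estimate

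*Protocol article*

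**What the plan says.** The Phase 2 part of the Analysis section sets the primary analysis as a mixed model, "using a generalized linear mixed model to account for matched pairs and random center effects". It then fixes the adjustment set: "The model will be adjusted for the number of encounters and other possible confounders not already matched". Two sentences later, the additional secondary and exploratory outcomes are to be modeled "adjusting for patient- and center-level confounders", without that restriction.

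The Control Group section describes the matching: "Intervention and control groups will be matched using the propensity score method". The score is a logistic model on patient-level variables (including age, sex, race and ethnicity, insurance, area income, diabetes duration, comorbidities and HbA1c) and center-level variables, among them "historical usage rates of CGMs and AID systems". The algorithm is greedy in form: "Nearest neighbor matching without replacement will be used, ensuring that each control patient is only matched once". Balance is judged covariate by covariate, "with a standardized mean difference of less than 0.1 indicating adequate balance". No step is given for a covariate that misses this limit. Sensitivity analyses use caliper matching, kernel matching and another matching ratio, and compare results with and without imputed values.

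**The concern.** A covariate can be treated as dealt with by matching only if the members of each matched set agree on it. Matching on a scalar score does not ensure this: two patients with the same score can differ on every component, and balance holds only on average and within tolerance.

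The other model terms do not close the gap. A matched-set effect leaves covariate differences within the set untouched. Random center effects cannot absorb imbalance between the groups, because the intervention is assigned by center.

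What is at stake is the primary estimate of a nonrandomized study. Imbalance on a variable that predicts uptake of the technology appears as intervention effect, in either direction, and the primary model as worded has no means of correcting it. The primary analysis also carries a narrower adjustment than the additional secondary outcomes.

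**Working it through.** The plan gives no figure for residual bias, so there is none to reproduce. The Power section supplies only a yardstick.

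**Inputs from the protocol article**
- Control progression 15%; smallest difference considered 5 points (Power)
- SMD limit 0.1; 1:4 matching (Control Group)
- About 3000 intervention patients in 7 centers and 15,000 possible controls in 41 centers (Results)

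**Assumptions (not in the document)**
- Binary covariate with prevalence p = 0.3 to 0.5
- Risk ratio RR = 1.5 to 3 for progression

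**Step 1. Bias from one covariate at the limit**

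Prevalence gap = 0.1 × √(p(1−p)): 4.58 points at p = 0.3 and 5.00 at p = 0.5.

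Covariate risk difference at a 15% mean: r0 = 0.15 / (1 − p + p × RR), and RD = r0 × (RR − 1). Bias = gap × RD.

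| p | RR | r0 | RD (points) | Bias (points) |
|---|---|---|---|---|
| 0.3 | 1.5 | 0.1304 | 6.5 | 0.30 |
| 0.5 | 1.5 | 0.1200 | 6.0 | 0.30 |
| 0.3 | 3 | 0.0938 | 18.8 | 0.86 |
| 0.5 | 3 | 0.0750 | 15.0 | 0.75 |

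The range is 0.30-0.86 points. That is 6-17% of a 5-point difference, and 2-6% of the 15-point difference that the Power section also names.

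**Step 2. Cross-check with a continuous covariate**

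In a logistic model with a 15% control rate, the bias when there is no true effect is:

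| Odds ratio per SD (assumed) | SMD 0.02 | SMD 0.05 | SMD 0.099 |
|---|---|---|---|
| 1.25 | 0.06 | 0.14 | 0.28 |
| 1.5 | 0.10 | 0.25 | 0.51 |
| 2.0 | 0.17 | 0.42 | 0.84 |

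At SMD 0.099 a true 5-point effect would appear as 5.35, 5.63 or 6.04 points. The two approaches agree, and the bias is roughly proportional to the SMD.

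**Step 3. How much room the matching has**

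At 1:4, 3000 patients use 12,000 of 15,000 controls, or 80%. For a normally distributed score (assumed), choosing the best 80% moves the control mean by at most φ(0.84)/0.8 = 0.35 SD. A gap before matching above about 0.45 SD could then not be brought under 0.1. The Power section speaks of 1:2 instead. That uses 40% of the pool, and the maximum shift is φ(0.25)/0.4 = 0.97 SD, so the pressure on balance depends on which ratio is used.

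**Step 4. Effect on type I error (two-sided 0.05 assumed)**

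Ignoring clustering, at 3000 versus 12,000 the standard error is √(0.15 × 0.85 × (1/3000 + 1/12,000)) = 0.73 points, and a 0.5-point bias raises type I error from 5% to about 10.5%.

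With equal center sizes and an intraclass correlation of 0.01-0.05 (assumed), the standard error is about 1.6-3.4 points. A bias of 0.3-0.86 points then gives about 5.1-8.3%. Because the planned model has random center effects, the second range is the more relevant one.

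**The case against.** Matching on some confounders and adjusting for the rest is a recognized strategy, and leaving matched covariates out of the outcome model is common. The plan also does more than match: it checks every SMD, inspects the score distributions before and after, and repeats the analysis with a caliper, a kernel and another ratio. A final covariate list may properly sit in an analysis plan that is not shown.

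Much of this stands as mitigation. It does not remove the point, because the article states a rule that takes the matched covariates out, and no planned analysis puts them back. Reading the restriction as meaning variables that remain unbalanced would help above 0.1, but the text does not say so, and imbalance below 0.1 would remain.

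Some stronger inferences are tempting and not supported:

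- **Several covariates adding up.** Four at the limit and aligned would give 4 × 0.30 to 4 × 0.86, or 1.2-3.4 points. Nothing in the document shows such alignment. Where it follows treatment assignment, it would also tend to show in the score, which the matching works on directly.
- **A bias that never shrinks with size.** This holds for systematic poor matching only. If patients were independent, the chance SD of an SMD would be √(1/3000 + 1/12,000) = 0.02, where the bias is 0.06-0.17 points. Covariates that cluster by center would vary more than this.
- **Baseline CGM status being excluded.** The matching list does not name it at patient level; it names center-level historical use. If it is unmatched, the present wording already admits it.
- **Adjustment removing most of the bias.** No calculation here shows how much it would remove.

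**Conclusion.** The point holds and is worth acting on, as a weakness in how the adjustment set is fixed rather than an error of arithmetic. The primary model, as worded, leaves residual imbalance in matched prognostic covariates in the estimate. One covariate at the accepted limit is worth about 0.3-0.9 points against a 5-point difference, under the assumed prevalences and risk ratios. That is an upper illustration for a single covariate, and it falls in proportion as balance improves.

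A reader might infer that the primary result would be seriously distorted, or that balance will fail. The document shows neither: achieved balance is unknown, and whether the 0.1 limit is hard to reach depends on the ratio and on the gap before matching. The case for change rests on a real gap with a near-free remedy.

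**What to change.** In the Phase 2 analysis text, delete the last three words of "The model will be adjusted for the number of encounters and other possible confounders not already matched" and prespecify the adjustment set of the primary model:

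- the main patient-level matching covariates: age, race and ethnicity, insurance, area income, diabetes duration and baseline HbA1c;
- patient-level baseline CGM status, named explicitly because the matching list does not name it;
- center-level historical CGM and AID use, as far as 7 intervention centers allow.

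Keep the number of encounters and the treatment, matched-set and random center terms. Show the model without the matched covariates as a sensitivity analysis.

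The matched variables are already collected. At 3000 patients and a 15% rate, about 450 events are expected in the intervention group before any effect, ample for this many patient-level terms. There is one small downside: in a logistic mixed model the conditional odds ratio changes with the covariates included. Report a marginal (standardized) risk difference alongside it, so that the adjusted and unadjusted results can be compared on one scale.

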**Objective:**

This study aims to develop and evaluate a best practice advisory (BPA) within the electronic medical record (EMR) to reduce racial and ethnic disparities in ADT use. We hypothesize that an EMR-based BPA designed to standardize the prescribing of ADTs will minimize racial and ethnic disparities in ADT adoption or progression in use among pediatric and adult people with type 1 diabetes.

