#### Intervention Centers

A total of 7 T1DX-QI clinical centers, consisting of pediatric and adult diabetes specialty clinics in the United States (Table 2), will participate in both the development and implementation of the BPA. A 7-item Qualtrics survey was distributed to all clinical centers within T1DX-QI to gather information on their EMR systems, capacity to develop automated alerts for CGMs and AIDs, IT capacity and commitment to the project, anticipated EMR freezes or delays during the planned intervention period, typical timeline for EMR changes at the institution, and previous experience building BPAs. Based on these responses, centers were selected to ensure geographical representation of the United States and a balance of pediatric and adult centers, with priority given to clinical centers using Epic EMR and demonstrating capacity, interest, and commitment to the project.

**Table 2 table2:** Intervention clinical centers.

Intervention center	Clinical center	Geographical region	Pediatric or adult
1	Johns Hopkins	Mid-Atlantic	Pediatric and adult
2	Hassenfeld Children’s NYU^a^	Northeast	Pediatric
3	Upstate Medical University	Northeast	Adult
4	Nationwide Children’s	Midwest	Pediatric
5	Grady Memorial	Southeast	Adult
6	University of Texas Southwestern	Southwest	Pediatric
7	Seattle Children’s Hospital	Northwest	Pediatric

^a^NYU: New York University.

Each center will have a designated principal investigator who will participate in monthly meetings with the organizing committee. Johns Hopkins University, which includes both pediatric and adult diabetes centers, will be the primary center for the development of the BPA. This center will oversee prototype development, testing, and postlive validation.

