#### Power

This study is powered to detect a between-group difference of 15% in the proportion of patients in the intervention and control groups meeting the primary endpoint. The matched-pair control assessment of 15% progression in ADT use is estimated from T1DX-QI data over a previous 12-month period. The largest sample size necessary for 90% power if the absolute difference in the proportion of ADT progression is only 5% (relative increase of 25%) is 589 matched pairs. If possible, we will attempt to match intervention to control patients in a 1:2 fashion with 2 matched controls per intervention patient. An interim analysis of the intervention group event rate may be conducted to inform whether additional matched pairs are needed.

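### The planned separate look at pediatric and adult centers gives no estimate of whether the effect differs between them, and the adult part rests on two or three intervention clinics (minor)

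*Protocol article*

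**What the plan says.** The Objective states the hypothesis for both populations: the advisory is expected to reduce disparities "in ADT adoption or progression in use among pediatric and adult people with type 1 diabetes". The primary analysis (Analysis, Phase 2) pools all centers, "using a generalized linear mixed model to account for matched pairs and random center effects". The only analysis that then distinguishes the two populations is one sentence in the same section: "Exploratory analysis assessing pediatric and adult centers separately will be performed".

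Intervention Centers describes "A total of 7 T1DX-QI clinical centers, consisting of pediatric and adult diabetes specialty clinics in the United States". Table 2 labels two as adult ("Upstate Medical University" and "Grady Memorial"), four as pediatric and one, Center 1, as both. The text below the table confirms this for Center 1: "Johns Hopkins University, which includes both pediatric and adult diabetes centers". No intraclass correlation, adult share of patients or subgroup power is given.

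**The concern.** Two separate analyses give two estimates and two p-values. Neither says whether the effects differ. The adult analysis has two or three intervention clinics against four or five in the pediatric one, so it is the less precise of the two even if the advisory works equally well in both. Each analysis also has to estimate the random center effects from only part of the centers.

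A split by center has no natural place for Center 1, which runs both kinds of clinic. Moving it changes the adult count from two to three.

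At stake is interpretation. A significant pediatric result beside a non-significant adult one invites the conclusion that the advisory helps only children, when the pattern may reflect nothing more than the number of clinics.

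**Working it through.** **The plan's own figure.** The documents give no figure for either subgroup. The 589 matched pairs under Power belong to the pooled analysis. The usual formula for two independent proportions (15% v 20%, two-sided 5%, 90% power) gives 1,212 per group. A McNemar calculation reaches 589 only with a discordant share of about 0.141, which is not stated. That is a separate matter and nothing below uses it.

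**Inputs from the documents.**
- Intervention clinics (Table 2): 5 pediatric and 3 adult if Center 1's two clinics are separated; 5 and 2 if Center 1 is all pediatric; 4 and 3 if all adult.
- 3,000 intervention patients and 41 control centers (Results).
- 1:4 matching (Control Group). Power mentions 1:2.
- Control progression of 15%, and differences of 15 and 5 points (Power).

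**Assumptions not in the documents.** Equal clinic sizes, 3,000/8 = 375 per clinic; control centers split 26 pediatric and 15 adult; ICC 0 to 0.05; two-sided 5% tests with normal critical values; the same true effect in both groups; independent tests; within-pair correlation ignored.

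**Formula.** For k_t intervention and k_c control clinics with n_t and n_c patients:

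Var = ICC × p0(1−p0) × (1/k_t + 1/k_c) + (1−ICC) × [p0(1−p0)/n_c + p1(1−p1)/n_t]

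Power ≈ Φ(difference/SE − 1.96). P(disagree) = P_ped(1−P_ad) + P_ad(1−P_ped).

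**Worked case: 15% v 20%, ICC 0.01, Center 1 separated.**
- Pediatric (5 v 26 clinics; 1,875 v 7,500 patients): 0.01 × 0.1275 × (1/5 + 1/26) + 0.99 × (0.1275/7,500 + 0.16/1,875) = 0.000304 + 0.000101 = 0.000405. SE 2.01 points, power 0.70.
- Adult (3 v 15 clinics; 1,125 v 4,500 patients): 0.000510 + 0.000169 = 0.000679. SE 2.61 points, power 0.48.
- P(disagree) = 0.70 × 0.52 + 0.48 × 0.30 = 0.51. Pediatric significant and adult not: 0.36. The reverse: about 0.14.

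About three quarters of the adult variance (0.000510/0.000679) comes from the few clinics, so more patients per clinic would help little.

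**Probability that the two tests disagree, identical true effect.**

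| True effect | ICC | 5 ped / 3 adult | 5 / 2 | 4 / 3 |
|---|---|---|---|---|
| 5 points | 0 | 3% | 12% | 4% |
| 5 points | 0.005 | 36% | 48% | 39% |
| 5 points | 0.01 | 51% | 56% | 50% |
| 5 points | 0.03 | 42% | 40% | 39% |
| 15 points | 0.01 | <0.1% | 0.4% | <0.1% |
| 15 points | 0.02 | 1% | 5% | 1% |
| 15 points | 0.05 | 21% | 35% | 24% |

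Spreading the 3,000 over 7 clinics instead (429 each) lowers the smallest ICC 0 figure, for 4/3, to 2%.

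**Sensitivity.** Using p1(1−p1) for the intervention clinics in the between-center term raises the 15-point figures at ICC 0.02 to 6% (5/3) and 16% (5/2). A t reference for few clusters would lower adult power somewhat further.

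**Comparison.** With identical effects, a test of the interaction declares a difference in 5% of trials whatever the ICC. A significant interaction together with a pediatric-only pattern occurs in at most 2.5%.

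**The case against.** The strongest reply is that the document plans nothing improper. The sentence is labelled exploratory, subgroup estimates are routine, and an interaction test is often left to an analysis plan that is not shown here. The hypothesis names children and adults as the population covered, and the pooled primary model covers both. No objective asks for an age contrast. All of this stands, and it keeps the point minor.

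Two stronger readings are tempting, and the documents support neither.
- A reader might infer that the separate analyses replace an interaction test, or that their p-values will be compared. The text does not exclude an interaction, and it plans no claim about a difference by age.
- A reader might infer that an equally effective advisory would often appear to work in children and not in adults. That depends on the true effect. The Power section describes the trial as "powered to detect a between-group difference of 15% in the proportion of patients in the intervention and control groups meeting the primary endpoint", and at that difference disagreement is rare for ICC up to 0.02. It is frequent near 5 points, which Power treats as the smallest case, once the ICC is above zero. Even there, disagreement includes the reverse pattern.

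Nor do the documents tie dissemination to subgroup results. The Discussion makes it depend on success in general.

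What the reply does not answer is narrower. The method named, a split by center, cannot estimate the difference between the groups, and one of the seven centers does not fit the split.

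**Conclusion.** The point holds as a minor improvement to a stated exploratory method. The adult analysis rests on two or three intervention clinics, Center 1 fits neither group as a whole, and no estimate of the difference is named. Across the three placements of Center 1, chance disagreement under identical effects is about 36-56% at 5 points for ICC 0.005-0.03 and about 2-12% at ICC 0. At 15 points it is about 0-5% for ICC up to 0.02 and about 21-35% at ICC 0.05. These figures rest on the assumed ICC, clinic sizes and control-center split, and on the variance form shown. They indicate scale and do not predict this trial's result. The primary analysis is unaffected.

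**What to change.** Obtain the pediatric and adult effects from one mixed model on the full matched cohort, with an intervention-by-clinic-type (pediatric or adult) term and the random center effects kept. Classify by clinic, so that Center 1's pediatric and adult clinics each enter their own group, and apply the same rule to control centers. Report both effects and the interaction with confidence intervals. State that no claim of effect in only one age group will rest on separate p-values.

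The cost is wording, with the same data and the same kind of model. The downside is a wide interaction interval. In the worked case its SE is √(2.01² + 2.61²) = 3.29 points, a 95% half-width of about 1.96 × 3.29 = 6.5 points. That width fairly describes what so few adult clinics can show.
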